## Research questions

1. Acceptability:
   1. What is the overall acceptability of Springfusor use among women with preeclampsia and eclampsia?
   2. What is the acceptability of the springfusor use for magnesium sulphate administration among health providers
   3. What is the level of pain associated with using Springfusor compared to the standard of care in administration of magnesium sulphate?
2. Effectiveness of Springfusor:
   1. What is the discontinuation rate of magnesium sulphate administration using a Springfusor pump compared to standard of care?
3. Safety
   1. What is rate of complications in the two arms?

Hypothesis

Use of Springfusor pump in the administration of magnesium sulphate in women admitted with preeclampsia and eclampsia is more acceptable than the hospital standard practice

Objectives

Primary objective

1. To compare the acceptability of the Springfusor pump to the standard of care in the administration of magnesium sulphate.

Secondary objective

1. To compare the proportion of complications between the Springfusor pump and the standard of care groups
2. To determine level of pain associated with using Springfusor compared to the standard of care?
3. To determine the discontinuation rate of administration of magnesium sulphate among women admitted with preeclampsia and eclampsia
4. To assess the reliability of Springfusor pump in the delivery of magnesium sulphate when used repeatedly
5. To assess the acceptability of the Springfusor pump for the administration of magnesium sulphate among the health providers.

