### Study procedure

Women with preeclampsia and eclampsia admitted at Mulago hospital maternal fetal unit will be screened and enrolled into the study if they meet the inclusion criteria. Both arms will receive the standard care as is currently given to women with preeclampsia in the health facilities; which includes management of high blood pressure, laboratory investigations (urine analysis, RFTs & LFTs) and delivery as planned by the attending physicians. Upon enrolment, study participants will receive the magnesium sulphate as per the randomization and any medication prescribed by the attending physician and received by the woman will be recorded in the CRF. The time it takes to administer the loading dose will be measured. Similarly the time it takes to administer the maintenance dose using the Springfusor will be measured using stop clock from the loading of the magnesium sulphate into device to completion of the medicine in the syringe.

The study participant’s respiratory rate will be monitored by the study midwives every 5 minutes during the loading dose (30 minutes). During the 24 hours maintenance dose, the participant’s respiratory rate, urine output and tendon reflexes will be monitored hourly. In addition, at four hourly interval, other side effects of magnesium sulphate like nausea, vomiting, flushing of the skin, muscle weakness, confusion and drowsiness will be noted. A report of pain and sign of inflammation will also be noted. The study participants will be followed till discharge and the women’s outcomes of the pregnancy will be reported. All women enrolled in the study will have an interview performed before discharge from the hospital. Study staff will administer a brief interview to capture information on the woman’s acceptability of magnesium sulphate using Likert scale, including the degree of pain experienced during administration of magnesium sulphate using a visual analogue scale. A standard operating procedure manual will be produced and provided to the study staff to enable adherence to the protocol.

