- *Feasibility of Springfusor pump use: ⃰* The proportion of women who have a Springfusor used for administration of magnesium sulphate and experience some technical problem with its use, blockage of FCT, the number of attempts made prior to successful Springfusor placement, the number of failed Springfusor placement and the number of FCTs and spilled magnesium sulphate used will also be documented.
- The *reliability** of the Springfusor to administer magnesium sulphate in the prescribed time will assessed for the loading period and the maintenance period. The intra-correlation coefficient for the device will be calculated.

These outcomes will be compared between the women in the two arms. A *outcome will be reported only for women who will have magnesium sulphate administered using Springfusor

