**Data analysis**

Data analysis will be performed by the PI. Descriptive statistics will be used to summarize baseline characteristics of study participants and assess if randomization was successful. The baseline characteristics will too give guidance as to which variables need to be adjusted for in the final analysis.

Acceptability and safety data will be evaluated using intention-to-treat (ITT) analysis. For comparing the maternal health outcome between intervention and control arms, the main analyses will look at the following variables;

1. Proportion of study participants who regarded magnesium sulphate administration using Springfusor or Pritchard route was acceptable. This will be compared using chi-square.
2. *Rate of complications of preeclampsia and its management:* Proportion of preeclamptic and eclamptic women who developed magnesium sulphate toxicity, abnormal liver and renal function test, infection at the injection and maternal deaths
3. The intensity of pain will be analysed using a ttest and presented as means and standard deviation
4. *Feasibility of Springfusor pump use:* The proportion of women who have a Springfusor used for the administration of magnesium sulphate and experience some technical problem with its use, blockage of FCT, the number of attempts made prior to successful Springfusor placement, the number of failed Springfusor placement and the number of FCTs used and spilled magnesium sulphate.
5. *The reliability of the springfusor:* The intra-class correlation coefficient (ICC) will be calculated. The closer the ICC to 1, the higher the reliability, ICC <0.4; the poor the reliability and ICC 0.4-0.75; the fair the reliability.

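### Pump reliability is timed to an empty syringe, so a maintenance infusion that never finishes cannot enter the reliability result

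*Protocol*

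**What the plan says.** The protocol's list of objectives (under Research questions) includes "To assess the reliability of Springfusor pump in the delivery of magnesium sulphate when used repeatedly". Outcome Measures turns this into the reliability "of the Springfusor to administer magnesium sulphate in the prescribed time will assessed for the loading period and the maintenance period", and Data analysis, item 5, names the statistic: "The intra-class correlation coefficient (ICC) will be calculated", with bands of below 0.4 (poor) and 0.4 to 0.75 (fair).

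Study procedure describes the measurement. For the loading dose it says only: "The time it takes to administer the loading dose will be measured". For maintenance infusions the clock starts when the device is loaded and runs "to completion of the medicine in the syringe". No other end point is given.

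Pump failures are recorded elsewhere. The feasibility outcome covers the proportion of women with a technical problem, and also "blockage of FCT, the number of attempts made prior to successful Springfusor placement, the number of failed Springfusor placement", the FCTs used and spilled drug. Data analysis repeats this as item 4. The discontinuation outcome counts doses received, and names the woman's choice, side effects and health workers' decisions as reasons for stopping. Feasibility and reliability are both reported for Springfusor women only.

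**The concern.** The stated question is whether the pump delivers the dose in the prescribed time. An infusion that never empties the syringe is the clearest case of not doing so, yet it is the case for which the measurement produces no value. An ICC, a mean or an on-time percentage built on these times describes only infusions that ran to completion. The values are missing because of the very property being measured, so the loss cannot be treated as random.

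This bears on how the trial will be used. The Justification says that favourable results may support scale-up of the device, and delivery on time over repeated use is central to that argument. If the form does not record, for each infusion, whether it finished and why not, a later analysis may be unable to separate a device failure from a stop for another reason.

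**Working it through.** **The plan's own figures.** The protocol states no reliability figure, so there is none to reproduce. Its sample size (219 per arm, 241 after allowing for non-response) concerns acceptability and does not enter this point.

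**Which infusions have a time**

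| Course of a maintenance infusion | Time under Study procedure | Enters the ICC |
|---|---|---|
| Runs to an empty syringe | Yes | Yes |
| Blocks, is cleared, then empties | Yes, a long one | Yes |
| Permanently blocked, or abandoned | None | No |

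For loading infusions the protocol gives no end point, so the table cannot be completed for them.

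**Do the other outcomes recover the third row?**
- Feasibility counts technical problems per woman, so one failed infusion and several in the same woman count alike. It also counts attempts, failed placements and FCTs used, but it sets none of these against the number of infusions started.
- Discontinuation does not name device failure as a reason. It sets a complete Springfusor course at 6 doses (24 gm), whereas Intervention gives 28 gm over 24 hours, and 28 / 4 = 7 infusions. On those two figures, a woman with one failed infusion in seven could still count as complete.

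**Number of infusions.** At most 241 x 7 = 1,687 on the Intervention figure, or 241 x 6 = 1,446 on the discontinuation figure. This sets the scale only; the percentages below do not depend on it.

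**On-time delivery.** Let c be the share of completed infusions that are on time and b the share of started infusions that never finish. A completed-only summary reads c. Over all started infusions the rate is c x (1 - b). The protocol gives neither quantity. Assume c = 0.95:

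| b | Completed only | All started |
|---|---|---|
| 2% | 95% | 0.95 x 0.98 = 93.1% |
| 5% | 95% | 0.95 x 0.95 = 90.25%, about 90.3% |
| 10% | 95% | 0.95 x 0.90 = 85.5% |

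**The ICC.** All inputs here are assumed: mean time 240 minutes, between-pump SD 15, within-pump SD 10, and a failed infusion set to 360 minutes (120 above the mean). For completed infusions only, ICC = 225 / (225 + 100) = 0.69. If pump i fails in a share p_i of its infusions, independently of its usual speed, then with E and Var taken over pumps:
- between-pump variance = E[(1 - p)^2] x 225 + Var(p) x 120^2
- within-pump variance = E[1 - p] x 100 + E[p(1 - p)] x (120^2 + 225)

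*Failures spread evenly, 5% in every pump.* Between: 0.9025 x 225 = 203.1. Within: 95 + 0.0475 x 14,625 = 789.7. ICC = 203.1 / 992.8 = 0.20.

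*9% overall, all in 2 of 20 pumps (90% in each).* Between: 0.901 x 225 + 0.0729 x 14,400 = 202.7 + 1,049.8 = 1,252.5. Within: 91 + 0.009 x 14,625 = 222.6. ICC = 1,252.5 / 1,475.1 = 0.85.

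Simulation with 20 pumps and 72 infusions each agrees: 0.67 falls to 0.20 in the first case, and 0.68 rises to about 0.85 in the second. The value of 360 minutes is arbitrary, so only the direction of each change is informative.

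**The case against.** The best answer is that the protocol nowhere says incomplete infusions are excluded, and that censoring or failure rules are commonly left to an analysis plan or an operating manual, neither of which is shown. The first part is true: exclusion is a consequence of the definition, not a stated rule. The second part does not dispose of the point. The gap lies in how the outcome is measured: the clock has one end point, and an infusion without it has no value to analyse. An analysis plan could add a rule, but only if the reason for non-completion was captured at the bedside.

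Three stronger readings are tempting, and the document does not support them.
- A reader might infer that the pump as a whole is judged on its successes. It is not. Feasibility, analysed directly before reliability, reports blockages, technical problems and failed placements, partly as event counts. Only the reliability result lacks the failures.
- A reader might infer that every blocked infusion is lost. A cleared blockage still yields a long time. In addition, the quoted end point is written for maintenance infusions and cannot be read across to the loading dose.
- A reader might infer that reliability is biased upwards whatever the summary. That holds for on-time delivery, where an infusion that never finished cannot have been on time. It fails for the ICC, as the two cases above show.

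It is also fair to say that the percentages rest on assumed inputs, and that an on-time proportion is not the statistic the protocol names. The proportion does, however, answer the outcome as Outcome Measures words it, whereas an ICC does not say whether delivery met the prescribed time.

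**Conclusion.** The point holds within limits. For maintenance infusions, secondary objective 4 is answered on completed infusions only, and the outcomes that do record failures are not tied to infusions started. An on-time summary of completed infusions overstates on-time delivery by c x b: 1.9, 4.75 or 9.5 percentage points at 2%, 5% or 10% non-completion, with c = 95%. Both inputs are assumptions. The direction is certain for on-time delivery but the size is not known. For the ICC the direction depends on whether failures cluster by pump.

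Reliability is a secondary outcome in one arm, so the primary comparison and sample size are untouched. The change should be made, but the trial does not depend on it.

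**What to change.** In Outcome Measures and Data analysis:
- Report, separately for loading and maintenance, the proportion of all started infusions delivered within a tolerance of the prescribed time that is fixed in advance. State the start and end of the clock for the loading dose.
- Count device-related non-completion as not delivered in time. List infusions stopped for other reasons separately.
- Keep the ICC only as a description of completed infusions, labelled as such.
- Reconcile the number of infusions in a Springfusor course: 7 follows from the 28 gm in Intervention, 6 from the 24 gm in the discontinuation outcome.

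On the infusion case record form, add a line for whether the infusion finished and, if not, why.

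The cost is one line on the form and a few sentences of protocol text. The reported reliability figure will be slightly less favourable.

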### Randomisation

A biostatistician at the Clinical Epidemiology Unit of Makerere University College of Health Sciences and not involved in the clinical trial will develop allocation sequence using an online computer random number generator in different block sizes. Women with preeclampsia and eclampsia will be randomized to have their magnesium sulphate administered with Springfusor pump or the hospital standard of care. The study participants will be randomized only after they have qualified for the study and signed informed consent. Serially numbered sealed opaque envelopes (concealed allocation) containing the randomization group will be provided at site in a secure place within the ward. Trained research staff will open the envelope to determine the group assignment after the participant is enrolled, completed all the baseline assessment and it is time to allocate the intervention

Blinding: Because of the nature of the study, it is difficult to blind the study, the implementation of the allocation and measurement of the outcome.

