### Outcome Measures

Primary outcome:

- Acceptability of Springfusor for administration of magnesium sulphate will be assessed using a Likert scale ranging from one (very acceptable) to five (very unacceptable). The method of magnesium sulphate administration is regarded acceptable if its rated 1 and 2 on the likert scale. It is not acceptable if the ranking is three and above. Women who discontinue the method of administration by choice or due to side effects will be considered in group of unacceptable.

Secondary outcomes:

- *Rate of complications of preeclampsia and its management:* Proportion of preeclamptic women who developed magnesium sulphate toxicity, abnormal liver and renal function test as reported by the laboratory report, infection at the injection as reported by the clinician and maternal deaths
- Discontinuation: This will be assessed as study participants who do not completed doses of magnesium sulphate in 24 hour period of including the loading dose. Participants who discontinue the method of administration by choice, due to side effects or by health workers decision will be considered in group. This will be measured by the number of dose received for each arm. For the Pritchard arm (standard of care), the number of complete 6 doses equivalent to 29 gm (including loading dose) in 24 hours. In the Springfusor, the number of complete 6 doses equivalent to 24 gm (including loading dose) in 24 hours.
- *Level of pain:* The study participants will be asked to assess the severity of pain during the administration of magnesium sulphate using Visual analogue scale 1-7. The least (one) representing no pain and maximum (7) representing the worst pain imaginable.
- Safety of use of Springfusor will be assessed by evaluating the possible occurrence of magnesium sulphate toxicity. This will be assessed by occurrence of any of the following
  - respiratory depression<16/min,
  - respiratory arrest,
  - depressed patellar reflex,
  - liver failure, renal failure,
  - cardiac arrest,
  - a need for calcium gluconate.
- In addition, other side effects of magnesium sulphate like nausea, vomiting, flushing of the skin, muscle weakness, confusion and drowsiness will be noted.

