## **Informed Consent**

The study midwives will obtain an informed consent from all participants enrolled into this study or the available relative as indicated above. All information that is given to the participant will be in a language that is understandable to her. If the woman is willing to participate she will be asked to read and sign the informed consent form. If the woman is unable to read, study staff will read and explain the form to the women, and the consent will be indicated by a mark, such as the woman’s thumbprint.

A copy of the signed consent form will be given to each participant. The original signed consent form for each participant will be kept at Mulago Hospital and in the participant’s study files separate from the CRFs. Study staff will be trained in the informed consent process. Women who decline to participate in the study will receive standard of care available at the site.

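### The deciding outcome is a subjective rating taken by study staff in an open-label trial, with no independent interviewer or private self-rating required

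*Protocol*

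**What the plan says.** - **Outcome.** Outcome Measures, primary outcome: "Acceptability of Springfusor for administration of magnesium sulphate will be assessed using a Likert scale". Scores of 1 or 2 count as acceptable and 3 or more as not acceptable. A woman who stops by choice or because of side effects is classed as unacceptable whatever she would have scored.
- **Collection.** Study procedure: "All women enrolled in the study will have an interview performed before discharge from the hospital", and "Study staff will administer a brief interview". The interview covers acceptability and also pain, which Outcome Measures puts on a 1-7 visual analogue scale. The protocol does not say who marks either scale.
- **Blinding.** Randomisation says that "it is difficult to blind the study, the implementation of the allocation and measurement of the outcome". No measure to limit the consequence for the outcome follows.
- **Who does what.** Informed Consent: "The study midwives will obtain an informed consent from all participants enrolled into this study". The same section uses the general term study staff for those who read the form to women who cannot read, and adds: "Study staff will be trained in the informed consent process". Study procedure has study midwives checking respiratory rate during the loading dose and names no role for the hourly maintenance checks. Setting says midwives give the medication. Data quality assurance has research assistants completing the case record forms.

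**The concern.** A rating of how acceptable a treatment was can depend on who asks. A woman still in hospital may give a kinder answer to someone who recruited her, gave her the drug or watched over her, and more so if she senses that the device is what the team is testing. Neither randomisation nor intention-to-treat analysis removes this, because it arises when the outcome is measured.

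The woman cannot be blinded, and the protocol says so openly. The identity of the interviewer and the privacy of the answer can be controlled, and the protocol fixes neither. For every woman who completes treatment, the interview alone decides whether she counts as a success on the outcome that decides the trial. No analysis can repair the bias afterwards.

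**Working it through.** **1. Is a safeguard stated?** Consent and loading-dose monitoring go to study midwives, and the interview goes to study staff. The second term is wide enough to include the first, and Informed Consent uses it for people who explain the consent form. No section requires a separate interviewer, private completion or a fixed script. Overlap is therefore open: neither stated nor ruled out.

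**2. The plan's own sample size.** Inputs from Sample size: 31% acceptability under the Pritchard regimen, 50% more in the Springfusor arm, power 90%, alpha 0.05, 10% non-response. I read the 50% as relative: 0.31 × 1.5 = 0.465, a difference of 15.5 points.

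- Two-sided, no continuity correction: n = [1.960·√(2·0.3875·0.6125) + 1.2816·√(0.31·0.69 + 0.465·0.535)]² / 0.155² = 205.5, so 206 per arm.
- With continuity correction: (205.5/4)·[1 + √(1 + 4/(205.5·0.155))]² = 218.2, so 219 per arm, as stated.
- 219 × 1.10 = 240.9, so 241 per arm, as stated.
- If 10% of 241 are not interviewed: 241 × 0.90 = 216.9, so 217 per arm.

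**3. Courtesy in the Springfusor arm only.** Assume no true difference (31% in both arms) and an observed Springfusor rate of 0.31 + b. The documents give no value for b, so a range is shown. With p̄ = 0.31 + b/2, the chi-square test without continuity correction rejects in favour of Springfusor with probability

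Φ{[b − 1.960·√(2p̄(1−p̄)/n)] / √[(0.31·0.69 + (0.31+b)(0.69−b))/n]},

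and the opposite tail is added. For b = 0.05 and n = 217 the two standard errors are 0.0453 and 0.0452, so Φ[(0.05 − 1.960·0.0453)/0.0452] = Φ(−0.86) = 0.196. The other tail adds 0.001.

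| Assumed inflation b | False positives, 217 per arm | False positives, 241 per arm |
|---|---|---|
| 0 | 5% | 5% |
| 3 points | 10% | 11% |
| 5 points | 20% | 21% |
| 8 points | 42% | 45% |
| 10 points | 58% | 63% |

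Five points means that 5/69 = 7.2% of the dissatisfied women in that arm switch their answer. Women who stop by choice or for side effects cannot switch, so the pool is smaller. If, as a further assumption, 20% of the arm stopped for those reasons, the same five points would need 5/49 = 10.2% of the rest.

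**4. Courtesy equal in both arms.** If a fraction c of dissatisfied women in each arm switch, each rate p becomes p + c(1−p) and the difference shrinks to (1−c) × 15.5 points. With no true effect the arms stay equal and the false-positive rate stays at 5%. With the planned effect and the plan's 219 per arm:

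| c | Observed rates | Difference | Power |
|---|---|---|---|
| 0 | 31.0% v 46.5% | 15.5 points | 91.7% |
| 10% | 37.9% v 51.9% | 14.0 points | 83.8% |
| 20% | 44.8% v 57.2% | 12.4 points | 73.9% |
| 30% | 51.7% v 62.6% | 10.9 points | 63.2% |

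**The case against.** - **Identity of the interviewer.** A reader might infer that the people who consented and monitored the woman also interview her. The protocol does not say this: it uses different terms for these tasks and names research assistants as a further role. Only the absence of a rule can be criticised.
- **Wording of the question.** A reader might take the outcome label, which names only the Springfusor, as the question put to women. It is a label. The next sentence of the same outcome refers to the method of administration, Study procedure speaks of acceptability of magnesium sulphate, and Data analysis covers both routes. A neutral script would follow wording already there.
- **Direction.** A reader might infer that the bias must favour Springfusor. The same interview is planned for all women, and courtesy in both arms dilutes the difference. A tilt towards the tested device is plausible but not established.
- **Size.** Every percentage in step 3 follows from an inflation I chose, set to zero in the control arm. Nothing in the documents supports a particular value.
- **Place.** A standard operating procedure manual is promised and not shown, and it might assign interviewers. Its stated aim is adherence to the protocol, though, and the protocol contains no such rule to adhere to.
- **Limits of any remedy.** Each woman knows her arm, another midwife is still unblinded, and reading aloud brings an interviewer back for women who cannot read. No staff numbers are given, so ease of rostering cannot be verified.

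These objections narrow the point. They do not touch its core: a subjective deciding outcome, open allocation and no stated safeguard in its collection.

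**Conclusion.** The point holds as an avoidable gap in how the outcome is collected. It is not a contradiction, and it is not evidence that biased interviewing is planned. The protocol leaves interviewer-related courtesy bias uncontrolled on its primary outcome and on pain. If the bias falls mainly on the Springfusor arm, an assumed shift of about a third of the planned effect (5 of 15.5 points) takes the false-positive rate from 5% to about 20% with 217 per arm. If it falls equally on both arms, false positives do not rise but power does fall, to between 83.8% and 63.2% when 10% to 30% of dissatisfied women switch.

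These figures rest on 31% control acceptability, a relative reading of the 50% increase, a two-sided chi-square test without continuity correction, and bias sizes that are assumptions. Classing women who stop by choice or for side effects without the interview limits the exposure but leaves every woman who completes treatment exposed.

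**What to change.** Amend Study procedure in three places:

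1. The woman marks both scales herself on a card, in private. A standard read-aloud version is used for women who cannot read.
2. The interview is rostered, from existing staff, to someone who did not consent, treat or monitor that woman.
3. One script is used in both arms. It asks about the way she was given magnesium sulphate and does not name the device.

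Sample size, treatment and analysis do not change. The cost is a response card, a script and some scheduling effort, most of it on thinly staffed shifts. Because the woman knows her arm, the bias is reduced and not removed, and the trial report should say so.
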